#### Secondary objectives

To assess the intervention effectiveness compared to usual practice as measured through self-reported continuous abstinence at 6 months.To assess the intervention effectiveness compared to usual practice in terms of the improvement in their quality of life measured by the EuroQol-5D-5 L questionnaire.To evaluate the cost-utility ratio of the intervention compared to usual practice in primary healthcare.To assess the intervention effectiveness in terms of improved adherence to pharmacological treatment for tobacco cessation.

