#### Design

The clinical trial will be pragmatic, randomized, controlled, and multicentric. It will last one year, six months for recruiting and six months of follow-up. A cost-utility study will be conducted from the perspective of the funder for a 1-year timeframe. (Figs. 1,2)

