#### Secondary outcome variables

Quality of life of the patient measured via the EuroQol-5D-5 L, a generic questionnaire in their Spanish version validated for our setting [21] that comprises two parts. The first part consists of five questions on the health condition of subjects to explore five dimensions: mobility, self-care, usual activities, pain/discomfort, and anxiety/depression. Each dimension is measured on a 5-level scale. From these five questions, a single weighed score is obtained, the so-called utility index. The higher the score the better the health condition. To obtain this index, the algorithm proposed for Spain has been employed [22]. The second part consists of a visual analog scale (VAS) ranging from 0 (worst possible condition) to 100 (best possible health condition). The intergroup differences in the utility score at 6 months will be used to construct the quality-adjusted life years (QALYs) gained with the intervention.

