#### Cost-utility

Costs derived from the intervention will be calculated via a proxy of their cost-opportunity. The price of avoided visits, calculated from the average salary of the health worker’s professional category, will be categorized as “saved costs”. An uncertainty threshold will be estimated for all the applied costs comprising the time range attributable to each activity. The calculation of benefits will be done based on the QALYs, quantifying the total gain from the EuroQol-5D-5 L utilities in the intervention group at 6 months and assuming they will stay constant for one year.

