#### Main effectiveness analysis

Intergroup differences in the continuous abstinence rates at 6 months (main variable) will be analyzed with their CI 95%. Bivariate analysis: a Student’s t-test, or the Mann-Whitney U-test in case the hypothesis of data normality is rejected, will be used to compare the outcome between groups in the case of quantitative variables. For qualitative variables, either Pearson’s chi-squared test or Fisher’s exact test, when applicable, will be used. After adjusting for possible confounding factors, the odds ratio of the association will be calculated using a logistic regression model where the dependent variable will be the continuous abstinence (yes/no) and the independent variables will be patient-related variables and the study group. In all cases, statistical significance will be set at *p* < 0.05. Gained QALYs will be estimated at a population level with their relevant CI 95% via parametric analysis methods and bootstrap techniques. Cost-utility ratio: this aim is exploratory (there is no specific design for it). The cost-utility ratio will be calculated dividing the overall cost by the sum of potential gains expressed in QALYs. For normally distributed data, a multivariate sensitivity analysis will be conducted, making the costs fluctuate within the constructed range of uncertainty. For the same distribution, we will also make the benefits (QALYs) fluctuate within the CI 95%. In all cases, the analysis will be for intention-to-treat. The number of withdrawals, losses to follow-up, and subjects not complying with the protocol will be recorded together with the relevant reasons. Losses to follow-up will be considered as smokers in the analysis [24]. A participant will be considered lost to follow-up after missing two appointments, failing to be contacted by phone in at least two occasions, and having no registered explanation for it. Missing information on professionals and/or patients will be replaced using values from the baseline data.

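### The exploratory cost-utility ratio is not written as a between-arm comparison, and its two QALY rules conflict

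*Protocol article*

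**What the plan says.** The aim under Secondary objectives is comparative: "To evaluate the cost-utility ratio of the intervention compared to usual practice in primary healthcare". Design sets perspective and horizon: "A cost-utility study will be conducted from the perspective of the funder for a 1-year timeframe".

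The ratio is defined under Main effectiveness analysis: "The cost-utility ratio will be calculated dividing the overall cost by the sum of potential gains expressed in QALYs". The same section calls this aim exploratory.

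The QALY gain is defined twice:

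- Secondary outcome variables: "The intergroup differences in the utility score at 6 months will be used to construct the quality-adjusted life years (QALYs) gained with the intervention".
- Cost-utility: benefits are obtained by "quantifying the total gain from the EuroQol-5D-5 L utilities in the intervention group at 6 months", and these utilities are carried forward, "assuming they will stay constant for one year".

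On the cost side, the Cost-utility section values avoided visits from average salaries and books them as savings. Under Variables there are two data-collection visits, baseline and 6 months. Under Employed time, consultations and minutes are recorded by the professional and by the chat-bot.

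**The concern.** A cost-utility ratio that compares two strategies needs the extra cost of one over the other, divided by the extra QALYs. Neither term of the written formula is stated as a difference between arms.

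The two QALY rules also answer different questions. One is a randomised comparison. The other, on its ordinary reading, is what happened in one arm, so it includes any change that would have occurred under usual care. That change cannot be presumed to be zero: controls receive active cessation care, and the sample size section expects 9.6% of them to be abstinent at 6 months.

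With two rules on paper, the same data yield two QALY results, and the choice could be made after the data are seen. A funder reading one cost-per-QALY figure would not know which comparison it represents.

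**Working it through.** The article gives no cost, utility or QALY figure, so there is no figure of the plan's to reproduce. The utilities and costs below are assumed, the costs in arbitrary currency units. They show how the rules behave and do not predict a result.

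**Notation.** gI and gC are the mean utility gains from baseline to month 6 in the chat-bot and control arms. Baseline utility is taken as equal, so the between-arm difference at 6 months is d = gI − gC. CI and CC are mean costs per patient.

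**Step 1: the two QALY rules, each held for a full year.** Rule A (Secondary outcome variables) gives d × 1. Rule B (Cost-utility, read as the gain within the intervention group) gives gI × 1. They differ by gC.

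| gI | gC | Rule A | Rule B |
|---|---|---|---|
| 0.02 | 0 | 0.020 | 0.020 |
| 0.02 | 0.01 | 0.010 | 0.020 |
| 0.02 | 0.015 | 0.005 | 0.020 |
| 0.02 | 0.02 | 0 | 0.020 |
| 0.01 | 0.02 | −0.010 | +0.010 |

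The rules agree only in the first row. In the last row they have opposite signs.

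**Step 2: the ratio.** Written ratio, taking the chat-bot arm's gross cost and Rule B: CI / gI. Incremental ratio: (CI − CC) / (gI − gC), on the same full-year basis.

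| CI | CC | gI | gC | Written | Incremental |
|---|---|---|---|---|---|
| 150 | 100 | 0.02 | 0.01 | 150/0.02 = 7,500 | 50/0.010 = 5,000 |
| 150 | 100 | 0.02 | 0.015 | 7,500 | 50/0.005 = 10,000 |
| 150 | 100 | 0.02 | 0.02 | 7,500 | extra cost 50, no gain: no finite ratio |
| 50 | 100 | 0.02 | 0.01 | 50/0.02 = 2,500 | saves 50 and gains 0.010: dominant |

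If the booked savings instead make the numerator a net cost equal to CI − CC, the first row becomes 50/0.02 = 2,500 against 5,000. The written ratio can therefore look worse or better than the incremental one, depending on the control gain and on what the cost term contains.

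**Step 3: accrual over the year.** Crediting the 6-month difference to the whole year gives 1.00d. A linear rise to month 6 followed by constancy to month 12 gives 0.5 × d/2 + 0.5 × d = 0.25d + 0.50d = 0.75d. The first is 1.00/0.75 = 1.33 times the second, or 33% higher. In the first row of Step 2 the incremental ratio moves from 5,000 to 50/0.0075 = 6,667. Within the 6 months observed, linear accrual gives 0.25d.

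**The case against.** The strongest defence is that the sections can be read together. Secondary outcome variables says the between-arm difference builds the QALYs gained. The gains named in the other two sections could be that same quantity summed over intervention patients, since Cost-utility mentions no baseline value. An avoided visit is avoided only relative to usual practice, so the cost side already has a comparative element. The aim is exploratory, one-year constancy is openly declared, and an article leaves computational detail to the full plan.

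Much of this stands, and it rules out several stronger readings that a reader might infer:

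- *That the analysis cannot answer the comparative question.* Both arms are measured, and the between-arm QALY rule and the booked savings could be combined into an incremental ratio. The defect is in the definition as written.
- *That the ratio is biased in the chat-bot's favour, perhaps several-fold.* Step 2 shows both directions, and any multiple depends on the assumed control gain.
- *That costs and QALYs are varied separately in the sensitivity analysis.* The article calls that analysis multivariate and says benefits will be varied as well as costs. It does not say separately.
- *That one-year constancy is itself an error.* It is a stated assumption matching the one-year horizon. Whether months 0 to 6 are credited in full is not settled, so the 33% belongs to one reading only.

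What the defence does not remove is the conflict. The article states both rules, one between arms and one within the intervention group, and gives a ratio that does not say which it uses. This is conflicting text, not detail left to a fuller document.

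**Conclusion.** The exploratory cost-utility analysis is defined inconsistently. Its aim is comparative, its ratio states no between-arm difference, and its two QALY rules, on their ordinary reading, agree only when the control arm gains nothing. The gap between the rules equals the control arm's gain (on a full-year basis, with equal baselines), which the documents do not give. Across the assumed cases it runs from zero to a reversal of sign. The written ratio can differ from the incremental one in either direction or hide dominance. The further 33% on QALYs applies only if the 6-month difference is credited to the full year and true accrual to month 6 is linear.

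This should be corrected, but its reach is modest: the primary outcome and the sample size are unaffected.

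**What to change.** Use one definition in Secondary outcome variables, Cost-utility and Main effectiveness analysis:

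- **Ratio:** (mean cost chat-bot − mean cost control) / (mean QALY chat-bot − mean QALY control).
- **Costs:** count visits and time in both arms, so that saved visits are the observed difference.
- **QALYs:** area under the curve from baseline and 6-month utilities in both arms, adjusted for baseline utility. This assumes the EuroQol is completed at both defined visits.
- **Horizon:** keep constancy over months 6 to 12 as a stated assumption, and show the 6-month within-trial result beside the one-year result.
- **Uncertainty:** bootstrap each patient's cost and QALY together. The article already names bootstrap for QALYs.

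The change is to analysis wording; the two visits and the recorded consultations and time should supply the data. The cost is slightly more analysis work and possibly a less favourable ratio.

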#### Variables

The collaborating healthcare professionals will deliver their data prior to the beginning of the study. The recruiting participants will record patient data and will be also responsible for their follow-up. All the information will be recorded on a form created for the trial (DCN). Each collaborator will access the form from their personal computer via the project’s website, using a code for personal identification. Two visits have been defined for data collection of patients: basal and at 6 months.

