#### Adherence to treatment

Number of weeks the patient gets pharmacological treatment prescribed by their doctor or nurse, as recorded by the professional in the DCN during each visit or automatically registered by the chat-bot.

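### As worded, baseline replacement sets a missing 6-month EQ-5D-5L score to no change, which biases the secondary quality-of-life and QALY comparison

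*Protocol article*

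**What the plan says.** All places are in the protocol article.

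- Main effectiveness analysis, last sentence: "Missing information on professionals and/or patients will be replaced using values from the baseline data". It carries no limit by type of variable or by visit.
- The same section has a separate rule for abstinence: patients lost to follow-up are counted as smokers. No other rule is given for missing EQ-5D-5L data.
- Variables: "Two visits have been defined for data collection of patients: basal and at 6 months".
- Secondary outcome variables: "The intergroup differences in the utility score at 6 months will be used to construct the quality-adjusted life years (QALYs) gained with the intervention".
- Cost-utility: the gain is taken from the utilities "in the intervention group at 6 months and assuming they will stay constant for one year".
- Main effectiveness analysis, on the interval: "Gained QALYs will be estimated at a population level with their relevant CI 95% via parametric analysis methods and bootstrap techniques". No step for imputation uncertainty is mentioned.
- Adherence to treatment is defined as "Number of weeks the patient gets pharmacological treatment prescribed by their doctor or nurse".
- The Discussion says that the quality-of-life assessment is not confirmatory, and the Main effectiveness analysis section calls the cost-utility aim exploratory.

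**The concern.** With only two patient visits, the only baseline value available for a missing 6-month utility or VAS score is that patient's own first score. Putting it in fixes the patient's change at exactly zero. The filled value then enters the group comparison, the within-group comparison across visits, and the QALY interval as if it had been measured. The Cost-utility section holds the 6-month utility constant to one year, so the imposed zero is carried forward as well.

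This is single imputation by baseline carry-forward, adopted as the main rule with no alternative analysis stated for it. At stake are the size, and under unequal loss the direction, of the quality-of-life and QALY difference.

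The sentence also fails on its own terms in two places. Weeks of medication has no baseline value to put in, and a baseline item that is itself missing cannot be replaced by itself.

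**Working it through.** **The plan's own figure.** The article gives no SD, expected effect or expected missingness for EQ-5D-5L. The figure that can be reproduced is the sample size. For 9.6% v 19.2%, two-sided 5%, 80% power, pooled variance:

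- Mean rate (0.096 + 0.192)/2 = 0.144.
- n per arm = [1.960·√(2·0.144·0.856) + 0.842·√(0.096·0.904 + 0.192·0.808)]² / 0.096² = 208.8, so 209 per arm and 418 in total.
- 418 × 1.10 = 459.8, so 460, or 230 per arm.

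Both figures agree with the article. The 10% loss is used below as the planned missing fraction; missing EQ-5D-5L forms could be more frequent than losses to follow-up.

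**Bias.** Let c1 and c0 be the mean true changes in the chat-bot and control arms, and d1 and d0 the fractions missing. Assume missingness is unrelated to baseline score or change, and that randomization gives equal expected baselines. Each filled patient contributes zero change, so

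expected difference = (1 − d1)·c1 − (1 − d0)·c0.

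*Equal loss d:* this is (1 − d) times the true difference. The factor is 0.90 at 10%, 0.80 at 20% and 0.70 at 30%. An assumed true difference of 0.030 becomes 0.027, 0.024 and 0.021.

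*Unequal loss (all inputs assumed):*

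| Changes (control / chat-bot) | Missing (control / chat-bot) | True difference | Expected under the rule |
|---|---|---|---|
| 0.03 / 0.03 | 10% / 20% | 0 | 0.80·0.03 − 0.90·0.03 = −0.003 |
| 0.03 / 0.03 | 20% / 10% | 0 | 0.90·0.03 − 0.80·0.03 = +0.003 |
| 0.04 / 0.04 | 40% / 20% | 0 | 0.80·0.04 − 0.60·0.04 = +0.008 |
| 0.02 / 0.05 | 20% / 40% | 0.030 | 0.60·0.05 − 0.80·0.02 = 0.014 |
| 0.02 / 0.05 | 40% / 20% | 0.030 | 0.80·0.05 − 0.60·0.02 = 0.028 |

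**Precision.** Assume a utility SD of 0.20, equal at both visits. Carry-forward keeps 230 per arm, so SE = 0.20·√(2/230) = 0.0187. Complete cases at 10% loss leave 207 per arm: 0.20·√(2/207) = 0.0197. The ratio is √0.90 = 0.949, about 5% smaller. At 20% loss it is √0.80 = 0.894. For change scores the ratio is nearer 1 − d, because the filled zeros also shrink the spread.

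**Coverage.** Simulation: 4,000 trials per setting, 230 per arm, SD 0.20, true difference 0.03, baseline to 6-month correlation 0.5 or 0.7, equal loss completely at random. The ranges span scores and change scores.

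| Missing in each arm | Coverage of the nominal 95% interval |
|---|---|
| 10% | 94–95% |
| 30% | 89–93% |
| 40% | 82–90% |

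At 10% loss and correlation 0.5, the SE reported by the rule on 6-month scores equalled the estimator's actual sampling SE (both 0.0187). The lost coverage at higher loss is therefore mainly a result of bias. A baseline-adjusted analysis of completers returned about 0.030 in each equal-loss setting with that true difference. Its SE at 10% loss was 0.0170, below the 0.0187 of the unadjusted carry-forward analysis.

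**The case against.** **The sentence may have been meant for covariates.** It names professionals together with patients. Professionals supply their data before the study starts, and the adjusting variables listed for them are all baseline items, so carry-forward has no meaning for that half of the sentence. This stands as a doubt about intention. It does not remove the problem: the text sets no such limit, and a missing baseline covariate cannot be filled from its own baseline value. If a group average at baseline is meant, the article does not say so.

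**Too narrow an interval.** A reader might infer that the intervals are invalid. The documents and the check do not support that at the planned loss. The interval is narrower only against the same analysis on complete cases, coverage at 10% is close to nominal, and the unadjusted interval can be wider than that of a baseline-adjusted model.

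**Unequal loss is not established.** Treatment contact differs by arm (chat-bot or face-to-face), but the data-collection visits are defined alike for both arms, and the primary outcome needs an exhaled-air reading at 6 months. Unequal loss is plausible in an unmasked trial, no more.

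**The outcomes are minor.** This stands. Quality of life is not confirmatory and cost-utility is exploratory.

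**Conclusion.** The concern holds for the secondary outcomes. As worded, the rule imposes no change on missing 6-month EQ-5D-5L utility and VAS scores, analyses them as observed, and passes the result into the one-year QALY. Under equal loss unrelated to change, the difference shrinks by the missing fraction: 10% at the planned loss, 20% at twice that. Under unequal loss the direction is open. Under-coverage becomes material only at about 30% loss or more. The rule is unusable for weeks of medication and for missing baseline values.

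Three stronger conclusions that a reader might draw are not supported:

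- That all missing patient data are affected, the main result included. Abstinence has its own rule, so the primary analysis is untouched.
- That the difference is always pulled towards zero. That is true for equal loss; the unequal-loss examples show false differences of either sign.
- That the distortion can decide the result. The false difference of 0.003 is 0.003/0.0187 = 0.16 standard errors at an assumed SD of 0.20, and the article gives no EQ-5D-5L SD, effect or missingness from which to argue more.

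The multipliers rest on missingness being unrelated to baseline score or change. The absolute figures and coverage rest on the assumed utility changes, SD and correlations.

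**What to change.** Replace the sentence with rules by type of variable:

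- **Abstinence:** keep the present rule that lost patients count as smokers.
- **6-month EQ-5D-5L utility, VAS, QALYs and weeks of medication:** state that baseline replacement does not apply. Analyse them with multiple imputation by arm, using baseline values and covariates, combined with the bootstrap for QALYs. For EQ-5D, a baseline-adjusted model valid under missing at random is an acceptable alternative.
- **Missing baseline covariates:** simple mean or multiple imputation.
- **Baseline carry-forward of EQ-5D:** report it only as a sensitivity analysis.

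The cost is a change of wording and some extra programming; no new data are needed. The main analysis of these outcomes would then rely on a missing-at-random assumption, which the carry-forward sensitivity analysis helps to probe.

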## Discussion

Both the healthcare professionals accepting to participate in a clinical trial and the recruited patients may be more interested in the subject of the trial, sharing an increased awareness and motivation for the studied health issues, which can lead to a bias. Although this can result in better outcomes compared to trials with less selective recruiting processes, it would have a conservative effect (namely, it would decrease the magnitude of the intergroup difference).

Additionally, participating collaborators may modify or improve their prescribing habits due to their awareness of being under observation (known as the Hawthorne effect). This may reduce differences between the intervention and control groups in terms of suitability of prescription.

A design by clusters was not chosen in this intervention, since the possible influence among smokers in the same healthcare center would be residual given that the app is personal and with a restricted access for the patient. This circumvents other biases resulting from variability in the clinical practice of included professionals and their basal knowledge on the subject of the intervention.

The intervention cannot be masked, so a blinded evaluation of the main outcome variable has been designed. The researchers in charge of the data analysis and interpretation will be unaware of the allocation arm of patients.

Although the assessment of the effect of the intervention on quality of life is not confirmatory and the expected changes are limited given the short period of time of the trial, we consider it essential to include this outcome variable in the analysis since intergroup differences can be detected even if they are not strongly significant. Additionally, measuring changes in quality of life allows for incorporating outcome variables that are self-reported by the patients, which facilitates the calculation of utilities in the cost-utility analysis. This will enable to overcome some deficiencies and limitations observed in previous interventions by Patterson et al. [24].

The chat-bot can potentially increase the effectiveness of the usual intervention for several reasons: on the one hand, it will provide primary care professionals with a very brief advice that will direct them to offer help for cessation [10], which has proven its high effectiveness for generating attempts to quit; on the other hand, it will at the same time reduce their workload, increasing their motivation to intervene on their patients. Additionally, the overall time employed in the dishabituation process would significantly increase, a variable that has been identified as one of the main predictors for continuous abstinence [2]; lastly, reminding and monitoring the use of pharmacological treatment will predictably improve adherence to it and, therefore, abstinence rates.

We estimate that this intervention will also show improved accessibility, since it enables people to access an effective program for quitting smoking even when physical limitations, schedule conflicts, or proximity issues exist that hinder face-to-face consultations.

On the other hand, our pragmatic design [25] will allow testing the usage of the chat-bot in conditions that closely mimic real life. Both the recruitment of patients and training of healthcare professionals, as well as the information given to patients and characteristics of healthcare centers, were the same in both arms. Other aspects denoting its pragmatic design were the criteria for inclusion, flexibility in applying the intervention, comparison with usual practice, absence of formal visits set by protocol, and intention-to-treat analysis.

It is essential to provide evidence on interventions directed to outpatients who smoke and that, owing to new information technologies, require less intervention by healthcare professionals. Given the spread of smartphones worldwide, there has been a great boom of apps that facilitate information on health issues and disease control and treatment. However, new approaches based on information and communications technologies appear at a much higher speed than controlled, high-quality trials.

The prediction is that this trend will increase due to the expanding number of users and the redundancy of different approaches to manage one’s healthcare on account of the new available functions of technological advances, so it is important to study why this is happening and remedy it in order to prevent ethical dilemmas and harm to patients. In order to help identify effective interventions, we strongly believe that clinical trials must be performed to evaluate new technologies and their related approaches to help smokers quit, just as they are performed for pharmacological drugs.

